### Outcomes

2.5

The primary outcomes (physical impairments) are as follows:

1.Pain will be measured using a 10 cm visual analogue scale (VAS) which 0 cm for “no pain” and 10 cm for “unbearable pain.” The VAS has been shown as a valid and reliable measure for assessing pain after TKA.^[38]^2.Knee swelling will be determined by measuring the knee circumference (1 cm proximal to the base of the patella) using a measuring tape. The value nearest 0.1 cm will be recorded. This outcome measure has excellent reliability on patients with TKA, with the smallest detectable difference of 1 cm.^[39]^3.A standard long-arm goniometer (EZ Read, JAMAR) will be used to identify any limitation of active knee range of motion with the participant positioned in supine. The participant will be asked to actively slide his/her heels on the bed to do knee flexion and extension, and the maximal active knee flexion and extension will be measured. The reliability of active knee range of motion measurement using goniometer was established in patients with TKA.^[39]^4.Quadriceps strength will be measured isometrically using a hand-held dynamometer (microFET 2, HOGGAN Scientific, LLC). The hand-held dynamometer had been used to assess change in quadriceps strength of patients with TKA in the previous studies.^[20,21]^ The measurement will be taken with the participant in supine position and the knee in 30° flexion (a roll of the towel will be placed under the knee). The hand-held dynamometer force pad will be placed proximal to the ankle joint. The participant will be asked to push against the dynamometer force pad as maximum as possible. The participants will perform two trials for 5 s hold per each trial and 30 s of rest between the trials. The knee extensor strength will be recorded in kilograms force which the higher peak force achieved between 2 trials will be used.^[20]^

The secondary outcomes are as follows:

1.Functional performance measuresTimed up and go (TUG) measures the time taken by a participant to complete rising from a chair, walking 3 m, and turning, walking back to the chair and sitting. The armed chair (seat height of 47 cm) will be used. The participant will be instructed to walk safely as quickly as possible. This test measures patients’ mobility with excellent reliability on patients following TKA.^[40]^11-step stair test will also be used to assess functional performance of the participant. This test will use a staircase with eleven steps (17 cm height steps with a depth of 30 cm and 110 cm width) with handrails on both sides, and a platform at the top and one at the bottom (110 cm by 140 cm). The participant will start the test with climbing up the stairs, turn around on the top platform, and climbing down the stairs, as fast as possible. The participants will be allowed to use 1 handrail if required. The time to complete the test will be recorded. This test has good reliability on the patient with TKA in measuring the physical performance of the patient.^[41]^Six-minute walk test will be used to measure how far the participants could walk in 6 min. The participants will be instructed to walk as far as possible on a level surface in 6 min and allowed to use an assistive device if necessary. The assessor will use a measuring wheel to record total distance covered. The participants could also rest for a while during the test as needed. This test has an excellent reliability in assessing functional performance of patients with TKA.^[42]^2.Quality of life will be assessed using the 5-level EQ-5D. This outcome measure has two parts which are the EQ-5D descriptive system and the EQ visual analogue scale (EQ VAS). The EQ-5D descriptive system consists of 5 dimensions which are mobility, self-care, usual activities, pain/discomfort and anxiety/depression. Each dimension has 5 levels of health state (level 1: no problems, level 2: slight problem, level 3: moderate problems, level 4: severe problems, and level 5: extreme problems). Besides, the EQ VAS has a vertical VAS which will be used by the participants to rate their health. The scale is numbered from 0 (worst health) to 100 (best health). The EQ-5D was used as the generic health measure for patients with TKA in previous studies.^[43,44]^ Besides, the Malays version of EQ-5D was shown can be used in Malaysia with the acceptable psychometric properties.^[45]^

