### Assessment of outcomes

2.6

Two days prior to TKA surgery, a researcher will verbally invite potential participants and briefly explain the purpose and procedure of the study before distributing the information sheets to them. At post-operative day 2, the participants will be further screened for eligibility and an informed consent will be obtained from patients who are eligible and agreed to participate. Once recruited, the socio-demography, information of height, weight and body mass index (BMI) of the participants will be recorded. The dose of analgesic medication used will be obtained from patients’ medical record (in-patient) and based on the patients’ report (out-patient).

All participants will undergo baseline assessments before allocated alternately into the two groups at post-operative day 2 for physical impairments, and quality of life following removal of drainage tubes and discontinuation of patient-control analgesia. Baseline assessment for functional performance will be performed at week 1 after the surgery.

Assessment of outcomes following intervention will be conducted at 4 assessment time points which are at week 1, 4, and 12 following TKA surgery and at 3-month follow-up (6 months after the surgery). Outcomes on physical impairments will be assessed at the end of week 1, 4, and 12 following the surgery and at 3-month follow-up. Whereas, outcome on the functional performance will be assessed at week 4 and 12 after the surgery and at 3-month follow-up. Finally, the interventions’ outcome on quality of life of the participants will be assessed at 3-month follow-up or 6-month post-surgery.

A trained physiotherapist who is blinded to the participants’ group allocation is responsible to conduct and record all assessments. To avoid recall bias, the recorded measurements of patient's pre-intervention status will not be accessible to others during the patient's post-intervention assessment.

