### Sample size

2.7

The sample size required for this study will be calculated based on the results of an ongoing pilot study. The pilot study involves 10 subjects per group; a sample size which is considered adequate to assess the effect size in a pilot study of clinical trial.^[46]^ The approximates of parameters, mainly effect size, obtained from the pilot study will then be inputted in G∗Power 3.1. ANOVA repeated measures, within-between interaction statistical test, with the number of groups and measurements 2 and 5 respectively will be used in the calculation. Level of significance is set at an alpha level of 0.05 and a statistical power of 80% will be chosen.

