### Data analysis

2.8

All data will be analyzed by the researcher using the statistical package for the social sciences (SPSS) 20.0 software, IBM Corporation. If missing data are identified, intention-to-treat will be used to ensure unbiased estimates of treatment effects between the two groups, and all participants who are recruited at baseline will be included in the outcome analysis.^[47]^

The characteristics of the participants will be presented in descriptive statistics. Mixed model ANOVA will be used to evaluate time, group and interaction effects of the interventions on participants’ pain, knee swelling, knee range of motion and quadriceps strength, as well as on the patients’ functional performance and quality of life. Further, multiple regression will be used to determine how much do recovery in physical impairments following low-intensity pulsed ultrasound as an adjunct to conventional physiotherapy influence the functional performance and quality of life of the patients. The level of significance is set as *P* < .05.

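### Knee swelling is a raw circumference first taken on post-operative day 2 with no reference value: change from day 2 can be compared, but remaining swelling cannot be measured and the group main effect carries limb size.

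*Protocol article*

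**What the plan says.** Section 2.5 lists knee swelling among four primary outcomes and defines it so: "Knee swelling will be determined by measuring the knee circumference (1 cm proximal to the base of the patella) using a measuring tape". Readings are recorded to 0.1 cm. On precision the article says: "This outcome measure has excellent reliability on patients with TKA, with the smallest detectable difference of 1 cm". The knee to be measured is not named, and no reference value is mentioned.

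Section 2.6 sets the timing. For the start: "All participants will undergo baseline assessments before allocated alternately into the two groups at post-operative day 2 for physical impairments". For follow-up: "Outcomes on physical impairments will be assessed at the end of week 1, 4, and 12 following the surgery and at 3-month follow-up". That makes five readings per participant. The only pre-operative contact described is an invitation: "Two days prior to TKA surgery, a researcher will verbally invite potential participants and briefly explain the purpose and procedure of the study". No measurement is attached to it.

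Section 2.8 gives the analysis: "Mixed model ANOVA will be used to evaluate time, group and interaction effects of the interventions on participants’ pain, knee swelling, knee range of motion". It adds a multiple regression of function and quality of life on recovery of the impairments. Section 2.7 sizes the trial on the interaction: "ANOVA repeated measures, within-between interaction statistical test, with the number of groups and measurements 2 and 5 respectively will be used in the calculation". The effect size and the main-study sample size await the pilot.

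**The concern.** Swelling is girth in excess of the participant's own unswollen knee. A raw circumference is limb size plus swelling, and the first one is taken when the knee is already swollen. With no pre-operative and no opposite-knee reading, the unswollen girth is never observed.

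Three things are at stake.

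- The group effect, which section 2.8 lists beside time and interaction, compares mean circumference and so takes in any chance difference in limb size between the groups.
- The same fall from day 2 can be complete resolution in one participant and partial in another, so remaining swelling cannot be reported.
- The regression objective in section 2.8 has to use change from day 2 or raw girth, and either may be a poor stand-in for the swelling a participant still has.

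**Working it through.** The article gives no SD, effect size or main-study sample size, so there is no planned figure to reproduce. The one usable input is the smallest detectable difference of 1 cm. If it is the usual 1.96 × √2 × SEM, then SEM = 1 / (1.96 × 1.414) = 0.36 cm and the error variance is 0.13 cm². All other SDs below are assumptions.

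**1. Does limb size disturb the planned tests?** One set of swelling data was simulated (30 per arm, five occasions, swelling SD 1 cm, treated group 0.7 cm lower at the four later occasions). A constant limb size per participant was then added, with SD 0, 2, 4 or 6 cm.

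| Limb-size SD (cm) | Interaction F | Group difference in mean level (cm) |
|---|---|---|
| 0 | 2.277411 | −0.60 |
| 2 | 2.277411 | −0.28 |
| 4 | 2.277411 | −1.64 |
| 6 | 2.277411 | −0.85 |

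The interaction is untouched. The group main effect moves by chance. The standard error that limb size alone adds to it is SD × √(2/30), which is 0.52, 1.03 and 1.55 cm for SD 2, 4 and 6 cm.

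**2. Power for a 1 cm difference** (two-sided 0.05, assumed 30 per arm, swelling SD 1.0 or 1.5 cm, within-person correlation of swelling 0.5). Change from day 2 has power 0.93 or 0.69 at every limb-size SD. Raw circumference at one visit has 0.40 or 0.34 at limb-size SD 2 cm, and 0.15 at 4 cm.

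**3. What would one opposite-knee reading add?** Model: day-2 operated knee = limb + asymmetry + swelling + error. Week 4 is the same limb and asymmetry, plus 40% of the day-2 swelling, plus other variation (SD 0.8 cm), plus error. The opposite knee = limb + error. Assumed: limb SD 2 to 4 cm, asymmetry SD 0.5 to 1.0 cm, day-2 swelling SD 1.5 cm.

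Worked case, limb SD 2 and asymmetry SD 0.5:

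- Var(day 2) = 4 + 0.25 + 2.25 + 0.13 = 6.63.
- Var(week 4) = 4 + 0.25 + 0.36 + 0.64 + 0.13 = 5.38.
- Covariance = 4 + 0.25 + 0.90 = 5.15.
- Adjusted for the day-2 operated knee only: 5.38 − 5.15²/6.63 = 1.38 cm².
- The opposite knee has variance 4.13 and covariance 4 with each operated-knee value, so it removes 4²/4.13 = 3.874 from each term above. This leaves 2.756, 1.506 and 1.276.
- Adjusted for both: 1.506 − 1.276²/2.756 = 0.92 cm², a 34% reduction.

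Over the assumed grid:

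| Week-4 contrast | Variance (cm²) |
|---|---|
| Simple change from day 2, operated knee | 1.71 |
| Simple change from day 2, operated minus opposite | 1.97 |
| Adjusted for day-2 operated knee | 1.38 to 1.60 |
| Side difference, adjusted for its day-2 value | 1.03 to 1.23 |
| Adjusted for day-2 operated and opposite knees | 0.92 to 1.09 |

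Adjusting for both knees saves 23% to 42% against the day-2 operated knee alone, and 37% to 46% against simple change (1.71 to 1.09 and 0.92).

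**4. Sensitivity.** Persistence was varied from 20% to 80% and day-2 swelling SD from 1 to 2 cm. Adjusting for both knees always helped, by 3% (0.923 to 0.892) up to 66% (2.92 to 1.00). The adjusted side difference ranged from 20% worse to 63% better.

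**5. Regression objective.** Under the step 3 assumptions, change from day 2 correlates only 0.08 in absolute size with the swelling present at week 4. Raw week-4 circumference correlates 0.23 to 0.43, and operated minus opposite 0.67 to 0.81.

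**The case against.** The strongest defence is that the planned analysis already deals with limb size. The knee is measured five times, the first time before allocation. Section 2.7 sizes the trial on the interaction, and section 3 speaks of comparing changes. A swollen day-2 knee is the natural starting point for a treatment begun that day. This stands. A reader might infer that the outcome cannot show recovery at all, but the documents do not support that: the fall in girth from day 2, and its difference between groups, can be estimated.

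A second tempting step is to redefine swelling as operated minus opposite girth. That does not stand either. In the planned change contrast it raises the variance from 1.71 to 1.97 cm², about 15%, because limb size has already cancelled and only tape error is added.

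Three more points hold in part.

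- Participants have knee osteoarthritis, so the opposite knee may not be normal.
- One-sided muscle change above the patella stays in the operated knee whatever is done with the other.
- A journal article is condensed, and the full protocol may name the side and a reference. Even so, the article's definition is detailed (site, tool, rounding, precision) and its visit schedule is complete, and neither contains a reference value.

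**Conclusion.** The concern holds in a limited form. As described, the swelling outcome supports comparison of change from day 2. It does not support a statement of how much swelling remains, or the use of remaining swelling as a predictor of function. The group main effect and single-visit levels are exposed to limb size.

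This is a moderate and correctable weakness in one of four primary outcomes, and it does not make that outcome invalid. The likely gain is a 23% to 42% lower residual variance, or about 3% to 66% over the wider assumptions. The direction was the same in every case run. The size rests on assumed SDs and persistence, and on limb size being stable to 6 months.

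**What to change.** - **Section 2.5:** state that the operated knee is measured. Add one reading of the opposite knee at the same level on day 2. Keep operated-knee circumference as the outcome.
- **Section 2.8:** name the treatment effect for swelling as the between-group difference in later operated-knee circumference, adjusted for the day-2 operated-knee and day-2 opposite-knee values, with covariate effects allowed to differ by visit. A constant covariate added only as a main effect would leave the interaction test unchanged. Do not read the unadjusted group main effect as a treatment effect.
- **Reporting:** give later operated girth minus the day-2 opposite girth descriptively as residual swelling. Flag participants whose opposite knee has been operated on or is swollen.
- **Section 2.7:** the calculation still awaits the pilot, so it can be matched to this contrast for swelling.

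The cost is about a minute with the same tape and assessor, plus protocol and case-report-form wording. Section 2.4 provides for justified amendments between pilot and main study. A day-2 reading not taken cannot be recovered later. The reference stays imperfect where the opposite knee is diseased, and one-sided muscle change is not removed.

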### Assessment of outcomes

2.6

Two days prior to TKA surgery, a researcher will verbally invite potential participants and briefly explain the purpose and procedure of the study before distributing the information sheets to them. At post-operative day 2, the participants will be further screened for eligibility and an informed consent will be obtained from patients who are eligible and agreed to participate. Once recruited, the socio-demography, information of height, weight and body mass index (BMI) of the participants will be recorded. The dose of analgesic medication used will be obtained from patients’ medical record (in-patient) and based on the patients’ report (out-patient).

All participants will undergo baseline assessments before allocated alternately into the two groups at post-operative day 2 for physical impairments, and quality of life following removal of drainage tubes and discontinuation of patient-control analgesia. Baseline assessment for functional performance will be performed at week 1 after the surgery.

Assessment of outcomes following intervention will be conducted at 4 assessment time points which are at week 1, 4, and 12 following TKA surgery and at 3-month follow-up (6 months after the surgery). Outcomes on physical impairments will be assessed at the end of week 1, 4, and 12 following the surgery and at 3-month follow-up. Whereas, outcome on the functional performance will be assessed at week 4 and 12 after the surgery and at 3-month follow-up. Finally, the interventions’ outcome on quality of life of the participants will be assessed at 3-month follow-up or 6-month post-surgery.

A trained physiotherapist who is blinded to the participants’ group allocation is responsible to conduct and record all assessments. To avoid recall bias, the recorded measurements of patient's pre-intervention status will not be accessible to others during the patient's post-intervention assessment.

### Sample size

2.7

The sample size required for this study will be calculated based on the results of an ongoing pilot study. The pilot study involves 10 subjects per group; a sample size which is considered adequate to assess the effect size in a pilot study of clinical trial.^[46]^ The approximates of parameters, mainly effect size, obtained from the pilot study will then be inputted in G∗Power 3.1. ANOVA repeated measures, within-between interaction statistical test, with the number of groups and measurements 2 and 5 respectively will be used in the calculation. Level of significance is set at an alpha level of 0.05 and a statistical power of 80% will be chosen.

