### Study design and setting

2.1

This is a quasi-experimental assessor-blinded study comparing two approaches of physiotherapy, namely Pulsed ultrasound-added physiotherapy group or control group with the participant's allocation ratio is 1:1. This study will be conducted at orthopedic wards and physiotherapy department in the Universiti Kebangsaan Malaysia Medical Centre, Kuala Lumpur, Malaysia. The flow of the study is shown in Figure 1. The process in this study will be first tested in a pilot study, following which a main study will be conducted.

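### The main trial's N will come from the effect size observed in a 3-week pilot of 10 per group, so the stated 80% power is not a property of the procedure

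*Protocol article*

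**What the plan says.** Section 2.7 (Sample size) gives no N for the main trial. It gives a rule for finding one: "The sample size required for this study will be calculated based on the results of an ongoing pilot study". On the pilot's size it says: "The pilot study involves 10 subjects per group; a sample size which is considered adequate to assess the effect size in a pilot study", with a reference. The rule continues: "The approximates of parameters, mainly effect size, obtained from the pilot study will then be inputted" into G*Power 3.1, using the repeated-measures ANOVA within-between interaction, "with the number of groups and measurements 2 and 5 respectively will be used in the calculation". The error rates are fixed too: "Level of significance is set at an alpha level of 0.05 and a statistical power of 80% will be chosen". Section 2.1 states that the "participant's allocation ratio is 1:1".

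Two other places bear on this. Section 2.4 (Interventions) says the pilot runs for 3 weeks. Section 2.6 (Assessment of outcomes) places the physical-impairment measurements at post-operative day 2, weeks 1, 4 and 12, and 6 months after surgery, which is where the five measurements come from.

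The article gives no target difference, confidence limit, shrinkage of the pilot estimate or minimum N.

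**The concern.** A power statement means something when the effect it refers to is fixed in advance. Here the effect is whatever 20 patients happen to show. The pilot estimate can go wrong in three ways:

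- **Imprecision.** With 10 per group, the estimate cannot separate no effect from a large one, so N is driven largely by chance.
- **Upward bias.** The interaction f is built from a ratio of sums of squares and has no sign. Noise alone makes it positive, and in small samples it overstates a true effect on average.
- **Wrong time window.** The calculation assumes five measurements over 6 months, but a 3-week pilot cannot observe week 4, week 12 or 6 months. A larger pilot of the same length would not cure this.

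At stake is whether the main trial can answer its question. A chance-large pilot effect leads to a small trial whose null result would say little. A chance-small one leads to an N that may not be recruitable.

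**Working it through.** The article states no N, effect size, SD, correlation or dropout rate, so there is no figure to reproduce. The check is whether the rule delivers 80% power.

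**Inputs from the article:** alpha 0.05, power 80%, pilot of 10 per group (18 between-subject error df), 2 groups, 5 measurements, 1:1 allocation.

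**Assumptions (not in the article):** true f of 0.15, 0.25 or 0.40; correlation 0.5 where the G*Power default scale is used; sphericity; no dropout; three measurements in the pilot (its assessment times are not given); the same true f in pilot and main trial.

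**1. Precision with 10 per group.** For a standardised difference d, SE = sqrt(2/10 + d²/40). At d = 0.5 this is sqrt(0.20625) = 0.454. The exact (noncentral t) 95% interval is -0.40 to 1.38. For a simple two-mean comparison, n per arm = 2 × ((1.960 + 0.842)/d)²:
- at d = 0.5, 15.70/0.25 = 62.8, so 63 per arm;
- at d = 1.38, 15.70/1.904 = 8.2, so 9 per arm;
- as d approaches 0, n grows without limit.

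**2. What f looks like when there is no effect.** Under the null and sphericity, interaction partial eta-squared with m measurements follows a Beta((m-1)/2, 18(m-1)/2) distribution. Its mean is 1/19 = 0.053 for any m, and f = sqrt((1/19)/(18/19)) = sqrt(1/18) = 0.236. The median f is lower: 0.16, 0.20 and 0.22 for 2, 3 and 5 measurements. Entering f = 0.236 with 5 measurements gives:
- G*Power default scale, lambda = f² × N × m/(1 - rho): total N = 24, lambda = (1/18) × 24 × 5/0.5 = 13.3;
- SPSS scale, lambda = f² × (N - 2) × (m - 1): total N = 58, lambda = (1/18) × 56 × 4 = 12.4.

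At the median null f for a 3-measurement pilot (0.20), the totals are 32 and 80. The article does not say which scale will be used.

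**3. Power delivered on the planned F test.** Pilots with three measurements were simulated (f on the SPSS scale). Each pilot's observed f was turned into a planned N for the five-measurement interaction test at 80% power, and the true power at that N was computed from the noncentral F distribution.

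| Assumed true f | Total N needed | Mean delivered power | Trials below 80% power |
|---|---|---|---|
| 0.15 | 136 | about 49% | about 76% |
| 0.25 | 52 | about 63% | about 63% |
| 0.40 | 22 | about 72% | about 55% |

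Repeat runs move these figures by a point or two. If the pilot had five measurements, mean power would be 41%, 59% and 71%: more measurements do not remove the shortfall.

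**4. Spread of planned N.** At true f = 0.25, where 52 patients are needed, the planned total N has a median of 36 and a 5th to 95th percentile range of 12 to about 398.

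**5. Inflation if the pilot SD is used instead.** The one-sided upper 80% limit of an SD on 18 df is SD × sqrt(18/12.86) = SD × 1.18.

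**The case against.** The strongest reply is that no N has been fixed, the pilot is still under way, and the article cites a reference for 10 per group. That reference cannot be checked here, and nothing in this point says it is wrong. The precision in step 1 follows from the sample size alone.

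A second reply is that the true f values are assumed. That stands, which is why a range is shown. Mean delivered power is below 80% across all of it.

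A third is that the error runs both ways. This also stands: some pilots will understate the effect and give an oversized trial. A reader might infer that the main trial will be underpowered. The documents do not support that. They support only that its power is left to chance and falls short on average.

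Three other stronger readings also fail:

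- A reader might take the swelling figure in section 2.5, "with the smallest detectable difference of 1 cm", as a worthwhile difference that the plan already has and ignores. It stands in a sentence on the reliability of the tape measure. It is a measurement-error figure, not a target between-group difference.
- A reader might ask how often the pilot would point the wrong way. That question belongs to a signed two-group comparison. The planned calculation uses f, which has no direction.
- A reader might see lost power or a raised false-positive rate in the no-effect case. With no true effect there is no power to lose, and the type I error of the main test is unaffected. That case shows only that noise can produce an ordinary-looking N.

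**Conclusion.** The point holds. Section 2.7 states a rule, not a detail left for later, and the rule does not have the power it claims: on average about 49% to 72% instead of 80% for true f between 0.15 and 0.40, with more than half of the resulting trials below 80%. These figures rest on the SPSS-scale f, a three-measurement pilot, sphericity, no dropout, and an equal true f in pilot and main trial. The last assumption is generous to the plan, because the pilot stops before three of the five measurements. The exact percentages depend on these choices. The conclusion that 80% is not secured does not, because it follows from the imprecision of 10 per group and the upward bias of f.

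**What to change.** In section 2.7:

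- Use the pilot only for feasibility, SD and the between-visit correlation for the visits it covers. Carry the SD's uncertainty forward, for example with its upper 80% confidence limit (SD × 1.18 at 18 df).
- Base N on a prespecified, justified worthwhile between-group difference in the primary outcome or outcomes that drive the calculation. Do not take the 1 cm in section 2.5 as that difference.
- If recruitment caps N, state the difference detectable at 80% power at that N.

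The edit is a short rewording and one recalculation, but the decision behind it is larger. Section 2.5 lists four primary outcomes, so the sponsor must choose and defend which of them sets N and what difference matters. The resulting N, or the detectable difference, may look less favourable. On the SPSS scale, a fixed f of 0.25 needs a total of 52 and a fixed f of 0.15 needs 136, both before dropout.
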